### **Mechanical Ventilation**

Ventilation according to the ARDSNetwork ARMA trial, which demonstrated a reduction in mortality using a tidal volume of 6 ml/kg PBW will be the standard of care [9]. Target tidal volumes will be  $\leq 6$  ml/kg PBW to maintain a plateau pressure  $\leq 30$ cmH2O. The recommended Positive End Expiratory Pressure (PEEP) will be based on the ARDSnet ARMA trial [9]. (See appendix 2)

Oxygenation will be titrated aiming for SpO2 of 88%-95% or PaO2 7-10kPa. Permissive hypercapnic respiratory acidosis aiming for a pH  $\geq 7.2$  is recommended.

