### 15.8 Adverse Event Reporting

As REALIST is recruiting in a population that is already in a life-threatening situation, it is expected that many of the patients will experience AEs. Events that are expected in this population (i.e. events in keeping with the underlying condition) should not be reported as AEs.

Examples of such adverse events include transient hypoxemia, agitation, delirium, organ failure, nosocomial infections, skin breakdown, and gastrointestinal bleeding. Such events will not be considered reportable adverse events unless the event is considered by the investigator to be associated with the study drug, or unexpectedly severe or frequent for an individual patient with ARDS.

The following pre-specified adverse events occurring within 6 hours of the start of infusion will be collected:

1. An increase in vasopressor dose greater than or equal to the following:
  - a. Norepinephrine: 0.1 mcg/kg/min
  - b. Epinephrine: 0.1 mcg/kg/min
  - c. Commencement of any vasopressor including norepinephrine, epinephrine, vasopressin, phenylephrine, and dopamine
2. New ventricular tachycardia, ventricular fibrillation or asystole
3. New cardiac arrhythmia requiring cardioversion
4. Hypoxemia requiring an increase in FiO2 of 0.2 or more and an increase in PEEP of 5 or more to maintain SpO2 in the target range
5. Clinical scenario consistent with transfusion incompatibility or transfusion-related infection (e.g. urticaria, new bronchospasm).

The following pre-specified adverse events occurring within 24 hours of the start of infusion will be collected:

1. Any death.
2. Any cardiac arrest.
3. Temperatures recorded as >38.5°C or temperatures that are recorded as >38.5°C prior to study drug administration and have increased by ≥1°C.

The investigator should attempt, if possible, to establish a diagnosis based on the subject's signs and symptoms. When a diagnosis for the reported signs or symptoms is known, the investigator should report the diagnosis as the AE, rather than reporting the individual symptoms.

The investigator should follow all AEs observed during the study until they are resolved or stabilised, or the events are otherwise explained.

All AEs should be treated appropriately. The action taken to treat the AE and the outcome will be recorded in the CRF.

All AEs, ARs and UARs should be reported on the AE Form within the CRF.

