**Appendix 2: ARDSNet PEEP/FiO2 Table**

|             |     |     |     |     |     |     |     |     |
|-------------|-----|-----|-----|-----|-----|-----|-----|-----|
| FiO2 | 0.3 | 0.4 | 0.4 | 0.5 | 0.5 | 0.6 | 0.7 | 0.7 |
| PEEP | 5   | 5   | 8   | 8   | 10  | 10  | 10  | 12  |

|             |     |     |     |     |     |       |
|-------------|-----|-----|-----|-----|-----|-------|
| FiO2 | 0.7 | 0.8 | 0.9 | 0.9 | 0.9 | 1.0   |
| PEEP | 14  | 14  | 14  | 16  | 18  | 18-24 |

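### Section 15.8 item 4: the pre-specified infusion hypoxaemia event cannot be met by any patient whose pre-infusion FiO2 is above 0.8

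*Protocol*

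**What the plan says.** Section 15.8 introduces a short list with "The following pre-specified adverse events occurring within 6 hours of the start of infusion will be collected". Item 4 is hypoxaemia requiring an FiO2 rise "of 0.2 or more and an increase in PEEP of 5 or more to maintain" SpO2 in the target range. The two conditions are joined by *and*, and no alternative is given for a patient who starts near the FiO2 ceiling.

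Outside that list, section 15.8 treats events in keeping with the underlying illness as not reportable: "Examples of such adverse events include transient hypoxemia, agitation, delirium, organ failure" and others. They become reportable only "unless the event is considered by the investigator to be associated with the study drug, or unexpectedly severe or frequent" for the individual patient.

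On ventilation, section 11.7 states: "The recommended Positive End Expiratory Pressure (PEEP) will be based on the ARDSnet ARMA trial", and points to the table in Appendix 2. It sets the SpO2 target at 88% to 95%.

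On monitoring, section 12.2 (Day 1) has FiO2, PEEP, oxygen saturation and plateau pressure recorded just before the infusion, every 15 minutes during it and hourly for 5 hours afterwards. Blood gases are recorded only if clinically available.

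**The concern.** A pre-specified list lets certain events be counted by a fixed threshold, without asking the investigator whether the drug or the disease was responsible. Section 14.3 reports these events descriptively in phase 2, and safety is the primary objective (section 5.3). Appendix 3 names hypoxaemia as a sign of two infusion reactions, hypersensitivity and leukoagglutination.

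Item 4 is the only entry on the list with an oxygenation threshold. If part of the population cannot satisfy it whatever happens to their lungs, they still sit in the denominator as patients without the event. A low or equal count could then be read as evidence of respiratory safety in a group where the definition could not have shown anything else. That group includes the patients with the highest oxygen requirement. The fallback is a judgement that hypoxaemia in severe ARDS was drug-associated or unexpectedly severe, and disease is the ready explanation.

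**Working it through.** The plan gives no event rate or count for item 4, so there is no figure of its own to reproduce. The check is arithmetic on the definition, set against the eligibility rules and Appendix 2.

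**1. Ceiling.** Item 4 needs final FiO2 ≥ starting FiO2 + 0.2, and final FiO2 ≤ 1.0. So starting FiO2 ≤ 1.0 − 0.2 = 0.8. A start at 0.85 would need 1.05, and a start at 0.9 would need 1.1. Neither exists. A start at exactly 0.8 can qualify, at 1.0.

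**2. Are such patients in the trial?** Section 8.3 sets no upper limit on FiO2. The Appendix 1 eligibility reference table runs to FiO2 1.00. Section 12.3 withholds bronchoscopy from patients receiving more than 80% oxygen, so the protocol expects them.

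**3. Appendix 2.** Four of the 14 settings (0.9/14, 0.9/16, 0.9/18 and 1.0/18–24, as FiO2/PEEP) can never meet item 4. For the other 10, I took an FiO2 rise of exactly 0.2 and the highest PEEP listed there:

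| Start | Highest PEEP at FiO2 +0.2 | PEEP rise | Item 4 met at FiO2 +0.2? |
|---|---|---|---|
| 0.3/5 | 10 | 5 | yes |
| 0.4/5 | 10 | 5 | yes |
| 0.4/8 | 10 | 2 | no; first at 0.7/14 |
| 0.5/8 | 14 | 6 | yes |
| 0.5/10 | 14 | 4 | no; first at 0.9/16 |
| 0.6/10 | 14 | 4 | no; first at 0.9/16 |
| 0.7/10 | 18 | 8 | yes |
| 0.7/12 | 18 | 6 | yes |
| 0.7/14 | 18 | 4 | no; only at 1.0 with PEEP ≥ 19 |
| 0.8/14 | 18–24 | 4–10 | only if PEEP ≥ 19 |

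Five of 10 starts qualify at exactly +0.2, and a sixth does if PEEP at FiO2 1.0 is at least 19. The other four need a larger move.

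Across the whole table there are 63 upward moves with FiO2 +0.2 or more (from 0.3: 11; 0.4: 18; 0.5: 16; 0.6: 5; 0.7: 12; 0.8: 1). Of these, 42 also give PEEP +5 or more when the 1.0 cell is held at PEEP 18, and 44 when it is taken at 24. That is 42/63 = 67% to 44/63 = 70%.

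**4. Size of the structural zero.** Let *p* be the share of patients starting above FiO2 0.8. The documents do not give *p*, so the values here are assumptions. Each cohort has 30 patients per arm (section 14.1), so 30*p* per arm cannot score:

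- *p* = 10%: 3 patients
- *p* = 30%: 9 patients
- *p* = 50%: 15 patients

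If comparable deterioration were equally common on both sides of 0.8, the reported incidence would be (1 − *p*) times the true one: 0.9, 0.7 or 0.5. Randomisation is stratified by centre and vasopressor use (section 10.2), not by FiO2, so the number unable to score can also differ between arms by chance.

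**The case against.** The strongest reply is that item 4 is one capture route among several. A reader might infer from the ceiling that acute lung harm in the sickest patients cannot register in this trial at all. The documents do not support that. Life-threatening hypoxaemia meets the SAE definition, and SAE incidence, not item 4, is the primary safety outcome (section 7.1). Lesser hypoxaemia is reportable if judged drug-associated or unexpectedly severe or frequent, and the last two grounds need no causal attribution. Section 15.8 also collects deaths and "Any cardiac arrest" within 24 hours, and within 6 hours "Clinical scenario consistent with transfusion incompatibility or transfusion-related infection (e.g. urticaria, new bronchospasm"), none with a ventilator threshold. The raw saturation and ventilator data exist for every patient. All of this stands. What is lost above FiO2 0.8 is the one oxygenation trigger that does not rest on judgement.

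A reader might also infer that the recommended PEEP/FiO2 table rarely yields the joint change, so that the item is close to void for everyone. The enumeration does not bear this out: 67% to 70% of table moves with FiO2 +0.2 or more satisfy both limbs. The table is also only a recommendation, and nothing in the documents shows how often patients make such moves within 6 hours. Below the ceiling, a strict rule fits the protocol's view of transient hypoxaemia as expected background. Replacing *and* with *or* for everyone would trade specificity for sensitivity, and no error compels it.

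Finally, the ceiling applies to both arms and clinicians are masked, so it does not systematically favour either arm. That is right. The cost is lost sensitivity and an incidence that is understated for the population as a whole.

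**Conclusion.** The point holds in this form: item 4 is arithmetically impossible for any patient starting above FiO2 0.8, and such patients are eligible. Following the rule exactly scores them as having no event. This is a fault in the rule, not detail left for the SAP. Their hypoxaemia then depends on investigator-judged AE or SAE reporting, with transient hypoxaemia excluded by default.

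The consequence is moderate. It affects one pre-specified secondary safety count, not the primary safety outcome, the efficacy analysis or the sample size. Its numerical size depends on the share of patients starting above 0.8, which is not stated. The range of 3 to 15 patients per arm rests on assumed shares of 10% to 50%. The impossibility itself rests on no assumption beyond the FiO2 ceiling of 1.0.

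**What to change.** Keep item 4 unchanged so that phase 2 remains comparable with phase 1. Add a supplementary derived event for patients whose pre-infusion FiO2 is above 0.8, met by either of the following:

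- SpO2 newly below 88%, the lower end of the section 11.7 target, at FiO2 1.0; or
- a fall in SpO2/FiO2 from the pre-infusion value by a relative margin fixed before unblinding.

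Both limbs are useful. With SpO2 unchanged, going from FiO2 0.9 to 1.0 lowers SpO2/FiO2 by 1 − 0.9/1.0 = 10%, and going from 0.85 lowers it by 15%. From a start at 1.0 only saturation can move the ratio, and a fall from 95% to 88% is 7/95 = 7.4%. The margin should be chosen with these limits in view. SpO2/FiO2 is preferable to P/F because blood gases in this window are taken only if clinically available.

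The inputs are already recorded under section 12.2. With infusions of about 30 to 90 minutes plus 5 hours, the scheduled readings run to between 5.5 and 6.5 hours from the start. The derived event should therefore state that it uses the readings available within 6 hours.

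Report item 4 by arm with the number of patients able to meet it (starting FiO2 0.8 or less) as the denominator, and give the number starting above 0.8 beside it.

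The cost is a sentence in section 15.8 and one derived variable. The downside is some background events in both arms, to be read against the placebo arm. The change concerns an event definition for analysis only and leaves patient management as it is.

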The following parameters will be recorded immediately prior to study drug administration and every 15 minutes for the duration of the infusion of study drug and every hour for the next 5 hours.

- FiO2, PEEP, oxygen saturation and plateau pressure as well as arterial blood gas pH, PaO2 and PaCO2 if clinically available.
- Heart rate, systolic and diastolic blood pressure, vasopressor doses.

Temperature will be recorded directly prior to study drug administration and will be recorded every 15 minutes for the duration of the infusion of the study drug and every hour for the next 5 hours.

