## **14 STATISTICAL CONSIDERATIONS**

### **14.1 Sample Size**

The phase 1 trial will recruit up to 18 participants.

Although the primary focus of the phase 2 trial is safety, there is, however, power to detect a difference in physiological outcomes.

The sample size for the phase 2 REALIST trial is 60 patients with ARDS due to COVID-19 and 60 patients with ARDS not due to COVID-19 (30 in each of the ORBCEL-C and placebo groups). The recruitment, randomisation, treatment, outcome measurement and reporting, and follow-up processes will be as streamlined as possible.

Due to the clinical differences in patients with ARDS due to COVID-19 and other causes of ARDS, patients with ARDS due to COVID-19 and other causes of ARDS will be recruited as separate cohorts. This will also facilitate timely reporting of the results from each cohort.

The primary efficacy outcome measure will be the difference in oxygenation index (OI) between the ORBCEL-C and placebo treated groups at day 7. Based on our data from a recently completed clinical trial in ARDS, the mean (standard deviation; SD) OI at day 7 in patients with ARDS is 62(51)cmH2O/kPa [4]. To allow 1:1 recruitment (ORBCEL-C vs placebo) a sample size of 56 subjects will have 80% power at a two-tailed significance level of 0.05 using a two-sample t-test to detect a clinically significant difference of 39 cmH2O/kPa in OI between groups. In a previous phase 2 study of similar size, we have found that an intervention can demonstrate a change in OI of a similar magnitude confirming a treatment effect of this size can be achieved [4]. Although we anticipate few withdrawals or loss to follow-up we have allowed for this in the sample size calculation. In previous UK multicentre studies in the critically ill <3% withdrew consent or were lost to follow-up [4, 65] and on this basis a conservative drop-out rate of 5% has been estimated. Therefore a total of 60 evaluable patients who have received study drug (30 patients in the ORBCEL-C and 30 in the placebo group) will be recruited into each cohort.

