## 14.3 Statistical Methods

For the Phase 1 trial no formal statistical analysis will be performed on safety data. The primary analysis will be descriptive and will focus on adverse events. The number of pre specified cell infusion associated events will also be reported. Descriptive analysis of pulmonary and non-pulmonary organ function will also be undertaken. We plan to publish the data from the phase 1 study.

The maximal tolerated dose up to 400x10^6cells will be proposed by the TMG and approved by the DMEC prior to use in the Phase 2 randomised controlled clinical trial.

For the Phase 2 trial, adverse events and prespecified cell infusion associated events will be reported as for the Phase 1 study in a descriptive analysis. For continuously distributed outcomes, differences between groups will be tested using independent samples t-tests and analysis of covariance with transformations of variables to normality if appropriate, or non-

parametric equivalents. Chi-square tests (or Fisher's Exact tests) will be used for categorical variables. A p value of 0.05 will be considered as significant.

Correlations between changes in the biological markers measured and physiological and clinical outcomes will be assessed by appropriate graphical and statistical methods including Pearson's (or Spearman's) correlation coefficient.

A final analysis and report of the Phase 1 study is planned following the last patient's 90 day follow up. A final analysis and report of the phase 2 study is planned following the last patient's 90 day follow up. The 2 year follow up data will be published thereafter and will be an important long term outcome. Detailed statistical analysis plans for phase 1 and phase 2 will be written and approved by the independent DMEC prior to any analysis.

All the power calculations and methodology for data analysis have been confirmed by the trial statistician from the Northern Ireland Clinical Trials Unit (NICTU).

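### The 24-hour fever event has a redundant second clause, so a fever that predates infusion and is recorded again afterwards counts as an infusion event even if it has not risen

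*Protocol*

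**What the plan says.** Section 15.8 lists three events under the lead-in "The following pre-specified adverse events occurring within 24 hours of the start of infusion will be collected": death, cardiac arrest and fever. The fever item reads "Temperatures recorded as >38.5°C or temperatures that are recorded as >38.5°C prior to study drug administration and have increased by ≥1°C".

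Other items in the same section are framed as a change from the patient's state before infusion. Examples are "New ventricular tachycardia, ventricular fibrillation or asystole", a new arrhythmia needing cardioversion, and stated increases in vasopressor dose, FiO2 and PEEP. The first clause of the fever item has no such condition, and no other section supplies one.

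The pre-infusion value is available. Section 12.2 (Day 1) says "Temperature will be recorded directly prior to study drug administration and will be recorded every 15 minutes for the duration of the infusion", and then hourly for five hours.

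On analysis, section 14.3 says that in phase 2 "adverse events and prespecified cell infusion associated events will be reported as for the Phase 1 study in a descriptive analysis". Section 14.1 sets each cohort at "30 patients in the ORBCEL-C and 30 in the placebo group".

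**The concern.** A definition with a special rule for patients who are already febrile should treat them differently from the rest. This one does not. The 1°C requirement has no effect, and stable or falling fever is recorded as a pre-specified infusion event.

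That matters because safety is the stated focus of phase 2. Section 15.8 also tells sites not to report events in keeping with the underlying illness unless they are linked to study drug or are unexpectedly severe or frequent. The pre-specified list is therefore the systematic record of possible infusion reactions, and Appendix 3 names fever among the signs of hypersensitivity. If the item picks up fever that was there beforehand, the two arms look more alike than they are. Sites may also differ in how they apply it, some following the literal text and some its evident intent.

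**Working it through.** **Step 1. The logic.** Let *b* be the temperature directly before study drug and *t* a temperature within 24 hours of the start of infusion.

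- Clause A: *t* > 38.5.
- Clause B: *b* > 38.5 and *t* − *b* ≥ 1.

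If B holds, then *t* ≥ *b* + 1 > 39.5 > 38.5, so A holds. *A or B* is therefore the same as A alone.

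**Step 2. Enumeration.** Take *b* and *t* each from 35.0 to 42.0°C in steps of 0.1, which is 71 values each and 71 × 71 = 5,041 pairs.

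- Clause A: 35 values of *t* (38.6 to 42.0) × 71 = 2,485 pairs.
- Clause B: 25 + 24 + … + 1 = 325 pairs.
- Clause B without clause A: 0 pairs.
- Already febrile, no 1°C rise, but still counted: 35 × 35 − 325 = 900 pairs.

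These are counts of possible combinations, not of patients. They confirm that B never adds an event and show which combinations A lets in.

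**Step 3. Effect on the comparison.** Let *f* be the share of patients who are above 38.5°C before infusion and are recorded above it again after the start, taken as equal in both arms. Let *p* be the rate of new fever in the rest.

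- Rate as written: *f* + (1 − *f*) × *p*.
- Difference between arms as written: (1 − *f*) × (*p*₁ − *p*₀).

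Patients in the share *f* are all events in both arms. They contribute nothing to the difference and add the same amount to both terms of the ratio, which moves it towards 1.

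**Step 4. Illustration.** The protocol states no figure for this event, so there is none to reproduce. All rates here are assumptions: 5% on placebo and 20% on cells, with a rise of at least 1°C in febrile patients as frequent as new fever in the others. A definition conditioned on pre-infusion temperature would then give 5% vs 20%, a risk ratio of 4.0 and a difference of 15 points, at every *f*. As written:

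| *f* | Placebo | Cells | Risk ratio | Difference |
|---|---|---|---|---|
| 5% | 0.05 + 0.95 × 0.05 = 9.8% | 0.05 + 0.95 × 0.20 = 24.0% | 2.5 | 14.3 points |
| 10% | 0.10 + 0.90 × 0.05 = 14.5% | 0.10 + 0.90 × 0.20 = 28.0% | 1.9 | 13.5 points |
| 25% | 0.25 + 0.75 × 0.05 = 28.8% | 0.25 + 0.75 × 0.20 = 40.0% | 1.4 | 11.3 points |
| 40% | 0.40 + 0.60 × 0.05 = 43.0% | 0.40 + 0.60 × 0.20 = 52.0% | 1.2 | 9.0 points |

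With 30 per arm and *f* = 25%, the expected counts are 30 × 0.2875 = 8.6 vs 30 × 0.40 = 12.0. Under the conditioned definition they are 30 × 0.05 = 1.5 vs 30 × 0.20 = 6.0.

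If only some pre-infusion fevers are recorded again, *f* is smaller and the dilution is less.

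**The case against.** The best defence is that the intent can be recovered. The item concerns events *occurring* after the start of infusion, and Table 3 defines an adverse event as an occurrence in someone who has been given the product. An unchanged fever that predates dosing is not naturally a new occurrence. Clause B has a purpose only if clause A was meant for patients who were not febrile beforehand. That is fair as a reading of intent. But the item does not say it, while its neighbours say *new* or *increase*, and a site following the text would record the event.

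It can also be said that no temperature data are lost. This is a capture rule, and the statistician can tabulate events by pre-infusion temperature. That stands, and it limits the severity. It does not make the stated definition correct, and wrong wording differs from detail left to an analysis plan.

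Three stronger readings are tempting, and the documents do not support them:

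- *That any fever before infusion counts.* It does not. The event must fall within 24 hours of the start, so a fever that settles and is not recorded again is outside the definition.
- *That the trial loses a quantifiable amount of power.* Section 14.3 plans only a descriptive report of these events, and the cohorts are recruited and published separately at 30 per arm, so a figure for 60 per arm matches no described comparison. At the assumed rates with *f* = 25%, Fisher's exact test at 30 per arm would have about 24% power undiluted and 9% diluted, poor under either wording.
- *That fever is the commonest infusion reaction, or common at baseline in these patients.* The protocol gives no frequency for either.

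**Conclusion.** The item is wrong as written. The redundancy of the second clause is a matter of logic and rests on no assumption. So does the consequence that a patient who was already febrile, and is recorded above 38.5°C again with no rise, counts as a pre-specified infusion event.

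The direction of the effect on the comparison, towards no difference, follows for fever that would persist whichever product was given, since randomisation spreads it equally in expectation. The size cannot be taken from the protocol. Risk ratios of 2.5 to 1.2 in place of 4.0 hold only for the assumed 5% vs 20%, for 5% to 40% febrile before infusion, and if all of that fever is recorded again.

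Severity is minor to moderate. This is one of several pre-specified safety items, it is reported descriptively, the primary safety outcome is serious adverse events, and the data needed to sort the cases are already collected. No claim about power is made.

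**What to change.** Reword the item in section 15.8 so that its two clauses cover separate patients by pre-infusion temperature, keeping the protocol's own values:

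- a temperature above 38.5°C in a patient who was at or below 38.5°C before infusion; or
- a rise of at least 1°C in a patient who was already above 38.5°C before infusion.

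Name the reference value as the one in section 12.2 (Day 1): "Temperature will be recorded directly prior to study drug administration". Carry the same rule into the case report form guidance and the derivation of the event.

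The cost is one sentence and one derivation rule, with no new measurement. For patients already enrolled, the event can be reclassified from the temperatures on record.
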